### Ethical Issues

Ethics approval for the RCT has been obtained from the Alfred Hospital Ethics Committee (project 18/18).

There is a small risk that participants will experience discomfort when answering questions about their alcohol consumption and its impacts, and reflecting on their previous weekend night. Participants do not have to answer any question if they feel uncomfortable about doing so.

There is also a small risk of participants feeling inconvenienced at having to answer hourly surveys on weekend nights. The impact is minimal given that the surveys will take only 1-2 minutes each. Participants are also be given the option at each hourly survey to opt out of completing subsequent assessments for that night.

Small payment will also be provided, as described above, to compensate participants for their time.

### Primary Outcome Measure

All measures were defined a priori. The primary outcome measure will be an observed change (ie, reduction) in the mean peak number of drinks consumed in a single night over the 6-week intervention period between those receiving the intervention (EMI) and attention control participants, as measured in the weekly EMA. This method improves on our previous study, which only collected this primary outcome measure at baseline and at follow up 12 weeks later.

The primary outcome measure is collected in the 11 am (next-day) survey on Sunday mornings each week during the 6-week study period (total of 6 measurements). The question asks participants to report on the highest number of alcoholic drinks consumed in a single occasion in the past week, and the night of the week alcohol was consumed. This measure will also be collected in a survey 12 months after commencement of the intervention period.

We expect to see a greater reduction in mean peak drinking in the EMI group compared to the attention control group. We also expect that the EMA group will show a reduction in mean peak drinking compared with that of the attention control group. The latter hypothesis is based on findings from our 2018 study, which showed a large but nonsignificant reduction in the EMA group compared to the control group [19]. We also expect to see a greater reduction in mean peak drinking in the EMI group compared to the EMA group.

It should be noted that this outcome is based on reducing peak consumption on a single occasion, rather than the general frequency or quantity of alcohol consumption over a period of time. This outcome is recognized as the most accurate measure of the key aim of binge-drinking interventions, namely to reduce the level of consumption (and harm) in an acute event. This single-item numerical measure has been shown to be reliable when compared to detailed time- and location-specific questioning across the drinking occasion [20].

### Secondary Outcome Measures

The following secondary outcomes of interest will be measured at the baseline, 6-week follow up (final Sunday 11 am survey), and 12-month follow up. Secondary alcohol consumption measures include annual consumption of >730 standard drinks per year (which equates to >2 standard drinks per day, in line with the Australian National Health and Medical Research Council guidelines for alcohol consumption) and, as two additional outcomes, monthly consumption of ≥5 and ≥11 drinks in a single session. These three measures will be derived from the graduated frequency measures, which include the following questions: “In the past 12 months, how often have you had 20 or more standard drinks in a day?” with response options including “Every day,” “5 to 6 days a week,” “3 to 4 days a week,” “1 to 2 days a week,” “1 day a week,” “2 to 3 days a month,” “About 1 day a month,” and “Less often than 1 day a month.” The question is then repeated with respect to the frequency of consumption: 11-19 standard drinks, 7-10 standard drinks, 5-6 standard drinks, 3-4 standard drinks, and 1-2 standard drinks. We will also examine changes in hazardous alcohol consumption using the Alcohol Use Disorders Identification Test [27].

We will measure experience of alcohol-related harms with yes/no/don’t know responses as to whether the participant has experienced different types of harm on their heaviest drinking occasion in the past 3 months, including: “Did you get into any verbal arguments or verbal fights on that occasion?”, “Did you fail to do what you intended to do the day after the session?”, and “Did you have any trouble getting home on that occasion?” These items were derived from the GenACIS [28] and VYADS questionnaires [29].

Usability and acceptability will be assessed in the follow-up survey among all groups using a 5-point Likert scale asking participants to rate a series of individual statements pertaining to their experience of undertaking the intervention (eg, “the assessments were easy to complete”). Additional process evaluation measures such as participant levels of response, refusal, and timeliness of response will also be explored to assess feasibility and acceptability.

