When an individual is deemed eligible to be enrolled in the study, researchers will invite them to participate using a standard script to describe the study (ie, all three groups will receive the same information about completing mobile phone surveys on Friday and Saturday nights for the next 6 weeks). If they provide verbal consent, the researcher will administer the baseline questionnaire over the phone on the spot. Reasons for refusal will be documented. Following completion of the interview, TKW Research Group will forward the details of new participants to the Burnet Institute, and we will send a welcome SMS text message with a link to detailed study information relevant to the participants’ assigned arm; this will include a plain-language summary of the procedures relating to their trial arm, additional information as per the usual requirements of an “explanatory statement” required by an ethics committee, as well as some frequently asked questions. Participants will be blinded to the purpose of the study. The nature of the intervention means it will not be possible to blind participants to their allocated arm; however, they will remain unaware of the detailed procedures of the other arms.

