### Event-Based Data Collection

#### Alcohol Ecological Momentary Assessment and Ecological Momentary Intervention Groups

Each participant from the EMA and EMI groups will fill out the same self-reported mobile phone–delivered surveys on Friday and Saturday nights for 6 weeks. In our previous studies [16,19], participants elected to complete the intervention on nights that they planned to drink. As the current trial includes an attention control (who are not exposed to alcohol questions or related content), this was not feasible, and we instead opted to predefine the intervention nights as the most popular drinking nights of young people based on our previous study. This was restricted to two nights to reduce the burden to the participants.

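### The three graduated-frequency drinking outcomes look back 12 months, so their 6-week readings are about 88% pre-intervention and cannot show the hypothesized effect

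*Protocol article*

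**What the plan says.** All references are to the protocol article.

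- **Timing.** Under Secondary Outcome Measures, the "secondary outcomes of interest will be measured at the baseline, 6-week follow up (final Sunday 11 am survey), and 12-month follow up".
- **Consumption outcomes.** One is "annual consumption of >730 standard drinks per year (which equates to >2 standard drinks per day"); the other two are monthly sessions of at least 5 and at least 11 drinks. "These three measures will be derived from the graduated frequency measures", and the item is worded "In the past 12 months, how often have you had 20 or more standard drinks in a day", then repeated for lower quantity bands. No shorter reference period is given for the 6-week survey.
- **Harms.** Participants report whether they "experienced different types of harm on their heaviest drinking occasion in the past 3 months".
- **Exposure.** EMI and EMA participants "will fill out the same self-reported mobile phone–delivered surveys on Friday and Saturday nights for 6 weeks".
- **Baseline.** At recruitment "the researcher will administer the baseline questionnaire over the phone on the spot".
- **Contrast.** The primary item, asked each Sunday, concerns "the highest number of alcoholic drinks consumed in a single occasion in the past week".

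**The concern.** An outcome read at the end of a 6-week intervention should mostly count what happened during those 6 weeks. These three consumption outcomes count a year. At the 6-week survey the window runs from about 46 weeks before the intervention to 6 weeks into it, and almost all of the earlier part was already reported at baseline. Whatever the intervention does, the 6-week answer should look much like the baseline answer in every arm.

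What is at stake is interpretation. A result of no difference on heavy drinking at 6 weeks is close to built in, and it could be read as evidence that the intervention leaves heavy drinking unchanged. The harm items share the problem to a lesser degree, because their window is 3 months.

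**Working it through.** **Inputs.** Intervention length is 6 weeks. Recall windows are 12 months (365.25/7 = 52.2 weeks) and 3 months (13.0 weeks). The annual threshold is 730 drinks. The hypothesized effect is 2.5 drinks from a mean of 13.2 with SD 5.2, and the within-person correlation is 0.52 (Effect Size and Sample Size). The lag from randomization to the first study night is not stated; I assume 0 to 2 weeks.

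**The plan's own figure.** 730/365 = 2.0 drinks per day, as stated.

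**Share of the window before the intervention, read at 6 weeks** (1 − 6/window):
- 12-month items: 6/52.2 = 11.5% after the start and 88.5% before.
- 3-month items: 6/13.0 = 46% after and 54% before.

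**Share strictly before randomization** (1 − (6 + lag)/window):

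| Lag (weeks) | 12-month items | 3-month items |
|---|---|---|
| 0 | 88.5% | 54.0% |
| 1 | 86.6% | 46.3% |
| 2 | 84.7% | 38.7% |

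**What the 12-month items can register.** A proportional cut *c* held for all 6 weeks moves a correctly answered annual total by *c* × 0.115.
- Full abstinence (*c* = 1): 11.5%.
- Hypothesized cut applied to volume (*c* = 2.5/13.2 = 0.19): 0.19 × 0.115 = 2.2%.
- Crossing the threshold: the highest starting total that abstinence could bring down to 730 is 730/(1 − 0.115) = about 825 drinks a year. Someone at 800 would need a cut of 70/(800 × 0.115) = 76%.
- Monthly sessions: someone with 12 heavy days a year who stops completely loses 12 × 0.115 = 1.4 of them. About 10.6 remain, which still fits the once-a-month response category.

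**Harm items.** The question picks out one occasion, the heaviest. As an illustration, take 13 weekly peaks, 7 before the intervention and 6 during it, normally distributed with within-person SD 5.2 × √(1 − 0.52) = 3.6. The simulated chance that the heaviest falls in the earlier 7 weeks is 54% with no effect, 66% if peaks fall by 1 drink, and 81% if they fall by 2.5. An effective intervention would push the harm answers further towards nights it could not have influenced. The size depends on the normal model; the direction does not need it.

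**At the 12-month survey.** The 12-month window lies essentially wholly after randomization. The 3-month window covers roughly months 9 to 12.

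**The case against.** The strongest reply has four parts.

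1. *Only secondary outcomes at one time point are touched.* This stands. The primary outcome uses past-week recall, six times, and neither it nor its sample size depends on these items. The effect is dilution towards no difference and favours no arm.

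2. *The article states no 6-week efficacy test of these items.* Its Statistical Analyses section deals with peak drinking, and the choice of time point for secondary inference may be settled in an analysis plan that is not shown. This stands in part: misreading a null is a risk, not something the article says it will do. But the article itself fixes both the item wording and the 6-week reading, and no analysis rule can make a 12-month question measure 6 weeks.

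3. *The 2% is a shift in true volume, whereas the outcomes are threshold classes built from coarse frequency categories.* This is correct, and the 2% should not be quoted as the bias in those outcomes. The limits on crossing 730 drinks or leaving a monthly category lead to the same conclusion. If respondents instead answer from recent weeks, the result is no longer the annual quantity it is labelled as.

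4. *The 12-month reading has its own dilution.* About 46 of its 52 weeks fall after the intervention has ended, so an effect confined to the 6 weeks would shrink by the same 88%. This stands: the 12-month comparison addresses a lasting effect.

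A reader might also infer that all 6-week secondary results are pulled almost entirely to zero, or that most harms counted predate randomization. The documents do not support either. For harms, 46% of the window lies within the intervention period, and with a lag of one week or more less than half is strictly pre-randomization. The Alcohol Use Disorders Identification Test cannot be included, because its recall period is not stated.

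**Conclusion.** The point holds for the three graduated-frequency outcomes at 6 weeks. About 88% of what they ask about precedes the intervention (at least 84.7% precedes randomization under a lag of up to 2 weeks). They cannot detect the hypothesized effect at that visit, and a null result there should not be taken as no effect on heavy drinking.

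For the 3-month harm items the dilution is partial, about 54% of the window, and is a limitation to state when they are interpreted. The primary outcome and the 12-month readings do not share this pre-intervention overlap, so the point gives no ground for doubting the trial's main comparison.

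The conclusion assumes that the 6-week survey uses the item wording printed in the article and that respondents answer it as worded.

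**What to change.** - Report the 6-week values of the three graduated-frequency outcomes as descriptive. Make their between-group comparison at 12 months, and describe it as a test of lasting effect.
- For heavy drinking during the 6 weeks, count the weeks with a reported peak of at least 5 and of at least 11 drinks, using the six Sunday reports. The Abstract places these in all groups, and the primary comparison with attention control requires them. Label the counts as supplementary to the primary outcome and as added after the measures were first defined.
- Keep the 6-week harm comparison, and state that about 54% of its window precedes the intervention. Moving harms to 12 months alone would discard the only reading whose window covers the intervention.

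**Cost.** A change of wording in the analysis plan and simple derivations, with no new data. Recruitment was complete by March 2019, so rewording the 6-week survey is probably no longer possible.

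**Downsides.** The derived counts dichotomize the primary item, so they are not independent evidence, and they replace neither annual volume nor harms. The weekly item is described as counting alcoholic drinks, whereas the graduated-frequency items count standard drinks, so the 5 and 11 cut-offs may not mean quite the same thing. Missed Sunday reports leave fewer weeks to count, so the number returned should be shown by arm.

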### Randomization

We will use Stata statistical software package version 15 (StataCorp LLC, College Station, TX, USA) to conduct block randomization to ensure balanced randomization to each of the three study arms. Randomization will be undertaken by a researcher external to the study team.

### Effect Size and Sample Size

We hypothesize that the intervention will result in a decrease of 2.5 drinks on peak drinking

occasions. In our recent cohort study [17] that utilized similar inclusion criteria, the mean number of drinks consumed on the “most recent big night out” was 13.2 (SD 5.2). Reducing this by a mean of 2.5 standard drinks (Cohen *d*=0.48) would halve the estimated odds of alcohol-attributable mortality, motor vehicle accidents, and other serious injuries in the population [30,31]. Previous work suggested that this effect size is achievable: a nonrandomized mobile phone intervention found a mean reduction of 2.1 drinks per session following an untailored SMS text messaging–based intervention from a baseline of just 5.2 drinks [3]. This change is also consistent with a meta-analysis of alcohol brief interventions which found a significant aggregate effect size improvement in alcohol consumption of 0.67 (95% CI 0.40-0.95) 3 months after intervention and 0.26 (95% CI 0.20-0.32) 12 months after intervention [32].

Assuming a standard deviation of peak drinking of 5.2, conservative 10% end-point attrition, 90% power, and conservative 1% type-I error rate, we estimate that a sample of 145 participants per group is required at minimum to detect an effect size of this magnitude.

The study sample size is based on the primary aim, the associated clinically meaningful difference, and the proposed analytical methodology, which includes multiple comparisons of effect across the three groups of the trial. The sample size estimate has been calculated to test for a linear group-by-time interaction (ie, a greater mean reduction in number of drinks across the 6 weeks for those receiving the intervention) from a random-effects mixed-model analysis (6 measurements) and moderate correlations between subject measurements (*r*=.52, estimated from the variance parameters from our 2018 study [19]. In case of additional attrition, we will aim to recruit 500 participants.

### Statistical Analyses

We will use a random-effects mixed-modeling approach using maximum-likelihood estimation to provide estimates of differences in peak drinking across time between those receiving the EMI and attention control participants. An intention-to-treat approach will be taken for this analysis. Initially, individuals and study groups will be modeled as random and fixed factors, respectively, in these mixed-model analyses. Appropriate fixed terms for the functional form of the association between study time and peak drinking will also be estimated in modeling. Additional analyses will explore the model fit of estimation of study group and time factors as random effects. The interaction between group allocation and study time is our primary focus. These analyses will be repeated, as secondary analyses, to determine the impact of the assessments alone (ie, comparison of EMA and attention control groups) using participant observations from the EMA group. Simple main effects for both treatment and time will also be estimated in the models. Distributional assumptions of models will be tested in the data and appropriate transformations applied in cases where these are not reasonably met. All statistical analyses will be performed using Stata statistical software package version 15.

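### The primary slope comparison starts from a participant random effect only and leaves random time effects to fit checks with no rule, so its type I error can exceed the 1% used for planning

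*Protocol article*

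**What the plan says.** The Statistical Analyses section makes the interaction of arm with time the main interest. The Effect Size and Sample Size section sizes the trial for a linear version of that interaction over six measurements. The primary test is therefore a difference in slopes.

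The model is described in two steps. The first is "Initially, individuals and study groups will be modeled as random and fixed factors, respectively, in these mixed-model analyses". The second is "Additional analyses will explore the model fit of estimation of study group and time factors as random effects". Nothing says how the result of the second step would change the primary analysis.

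For planning, the Effect Size and Sample Size section uses a "conservative 1% type-I error rate" and one common within-person correlation of .52, taken from the variance parameters of the 2018 study. It gives no between-person variance of slopes and no figure for how correlation falls with the gap between weeks.

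**The concern.** A random intercept alone carries two assumptions: every pair of weeks has the same correlation, and all participants in an arm share one time slope. For a difference in average level these often do little harm. For a difference in slopes they matter directly. If some participants drift up and others down, the average slope in an arm is less certain than the intercept-only model reports. Serial correlation between neighbouring weeks acts in the same direction. The model then gives a standard error that is too small, confidence intervals that are too narrow, and more false-positive results than the nominal level. In the large-sample calculation the ratio of reported to true standard error does not depend on the number of participants, so recruiting 601 instead of 500 does not cure it.

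The term that guards against this, a participant-level random effect of time, is the one placed among the additional fit analyses. With no selection rule, the primary p-value could come from either model after both have been seen.

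The support for equal correlation is also thin. The Primary Outcome Measure section describes the earlier study as one "which only collected this primary outcome measure at baseline and at follow up 12 weeks later". Two time points cannot show the pattern across six weekly ones.

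**Working it through.** **Inputs from the article.** "Assuming a standard deviation of peak drinking of 5.2"; correlation .52; six weekly measurements; 1% type I error; 90% power; difference 2.5 drinks; "conservative 10% end-point attrition". Sidedness is not stated. **Assumed:** equally spaced weeks, complete data, and the values of the slope SD and of the serial correlation.

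**Step 1: the plan's own figure.** The article states that "a sample of 145 participants per group is required at minimum". For two means, n = 2(z₀.₉₉₅ + z₀.₉₀)² × (SD/difference)² = 2 × (2.576 + 1.282)² × (5.2/2.5)² = 128.7, so 129. Dividing by 0.9 gives 143.3, so 144. Using d = 0.48 gives 130, and 130/0.9 = 144.4, so 145. The stated figure is reproduced as a two-sided comparison of two means; one-sided gives 126 and does not fit. A slope test under equal correlation gives 99 if the 2.5 drinks accrue over five weekly intervals and 143 if they are scaled to six, so the origin of 145 is not unique. None of these versions contains a slope variance.

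**Step 2: variance of a participant's slope.** Residual variance: 5.2² × (1 − .52) = 12.98. Weeks 1 to 6 have sum of squares about their mean 17.5. Let b be the SD of true individual slopes in drinks per week.

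- True variance of one estimated slope: b² + 12.98/17.5 = b² + 0.742.
- Variance reported by the intercept-only model: slope variation leaks into the residual, which becomes 12.98 + b² × 17.5/5. Divided by 17.5 this is b²/5 + 0.742.

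The ratio of reported to true standard error is the square root of the second over the first. The actual error at nominal 1% is 2 × [1 − Φ(2.576 × ratio)].

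| Slope SD b | True variance | Reported variance | SE ratio | Actual error |
|---|---|---|---|---|
| 0 | 0.742 | 0.742 | 1.00 | 1.0% |
| 0.2 | 0.782 | 0.750 | 0.98 | 1.2% |
| 0.5 | 0.992 | 0.792 | 0.89 | 2.1% |
| 0.75 | 1.304 | 0.854 | 0.81 | 3.7% |
| 1.0 | 1.742 | 0.942 | 0.74 | 5.8% |

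**Step 3: simulation.** With 10,000 runs per value and 130 per arm, the intercept-only test rejected in 1.1% of runs at b = 0, 1.3% at 0.25, 2.4% at 0.5, 3.8% at 0.75 and 6.0% at 1.0. A test based on each participant's own slope, which is what a random slope delivers in balanced data, stayed between 1.1% and 1.2% throughout.

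**Step 4: serial correlation instead of varying slopes.** With a random intercept plus AR(1) residuals of variance 12.98, the actual error is 1.6% at a residual correlation of 0.1, 2.4% at 0.2 and 3.4% at 0.3. As an extreme case, pure AR(1) with correlation 0.734 averages .52 over all pairs of weeks and gives an SE ratio of 0.64 and an actual error of 10%.

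**The case against.** The strongest reply is that the article does not fix the random-intercept model as the final test. It calls it the initial model and announces a look at random time effects, so the final model may well contain them. That stands. A reader might infer that the primary result will come from random intercepts only, and the text does not go that far. What it does is leave the choice open, with no rule, for the term that a slope test most needs.

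A second reply is that the inflation is conditional. That also stands. A reader might infer that the error rate does exceed 1%. The documents give neither slope variance nor serial correlation, and with neither present the test is valid. At a slope SD of 0.2 or less the effect is negligible. A slope SD of 1.0 means that trends over five weekly intervals vary with an SD of 5 drinks, close to the whole cross-sectional SD of 5.2. The 10% case has no stable between-person component and implies a correlation of only about .21 between weeks 1 and 6 (0.734⁵). It marks an outer limit and should not be quoted as the expected error.

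Third, the 1% is a planning input; the Statistical Analyses section states no test level. It should be described as the level used for sizing, although it is the only error rate in the article and it was set for this interaction.

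Fourth, that the .52 rests on two time points is a reasonable inference, not a stated fact: participants in the 2018 study also completed the intervention or assessments on six nights.

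Finally, covariance details are often left to an analysis plan, and that plan is not shown. The point here is not that detail is absent. The article states an order of models and puts the random time effect in the secondary place.

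**Conclusion.** The concern holds in conditional form. The article starts its primary slope analysis from a participant random effect only, places random time effects among additional fit checks, and gives no rule for which model yields the primary result. If the intercept-only model is used, the actual error at nominal 1% runs from 1.0% to 5.8% for assumed slope SDs from 0 to 1 drink per week, and from about 1.6% to 3.4% for assumed residual AR(1) correlations of 0.1 to 0.3. Where either feature is present, the departure is towards false positives. The figures assume SD 5.2, r = .52, six equally spaced weeks and complete data.

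The proposal to try study group as a random effect is a smaller matter. Two or three deliberately chosen arms cannot usefully estimate a variance. A reader might infer that the reported treatment contrast would be shrunk, but the initial model keeps group fixed and the random version is only an exploration.

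Severity: should-fix.

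**What to change.** Before analysis, name one model as the source of the primary interaction estimate and p-value. Either of these would serve:

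- an unstructured 6 × 6 within-person covariance; or
- a participant random intercept plus random time slope with unstructured covariance between them, and participant-clustered robust standard errors, which also protect against remaining serial correlation.

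Keep study group as a fixed effect in every model, and drop the exploration of group as a random effect.

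The change is to the model specification and needs no further data. The price is wider standard errors, and hence lower power, to the extent that slopes vary or serial correlation is present. From the table, the true standard error exceeds the intercept-only one by about 12% at a slope SD of 0.5 (√(0.992/0.792) = 1.12) and about 36% at 1.0 (√(1.742/0.942) = 1.36). If slopes do not vary and there is no serial correlation, almost nothing is lost.

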In the past five years, focus has been placed on ecological momentary interventions (EMIs), which aim to deliver the intervention content in correspondence to real-time assessments of behavior, also known as ecological momentary assessments (EMAs) [14]. The difference between EMI-based studies and the aforementioned mobile phone–delivered alcohol intervention studies is the act of interrupting the drinking event in the moment it occurs. EMIs frequently feed off information provided in EMAs, allowing for the intervention to be specifically tailored to the individual’s circumstances at the time. The combination of these two factors allows for a highly salient interruption at a time most pertinent to the recipient [14,15]. In our previous work, young adults likened the experience of receiving EMI to having a sober friend or a sober version of themselves pull them out of a drunken haze and gently tweak their behavior to help them avoid going “too far” [16].

Riordan et al [8-10] have focused on EMI for university students, particularly during the orientation week period. In two separate studies, they tested the effect of sending EMAs and EMIs during orientation week, and throughout the university semester; these EMIs were developed specifically for the student population and were informed by formative research. Their results have been mixed, with one study showing an effect in females but not males [8] and a second study showing an effect in one college but not another [9]. Although Riordan et al [17] highlighted a key risk group for alcohol consumption and related harm, many other nonstudent young adults also drink to excess regularly. Therefore, there is a need to test EMIs that focus on more general populations of young adults.

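### The primary group-by-time test uses six reports that all follow the start of intervention, so it has no power for an effect complete at the first report and sustained

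*Protocol article*

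**What the plan says.** Under Statistical Analyses, the comparison of the intervention (EMI) arm with attention control rests on a random-effects mixed model, and "The interaction between group allocation and study time is our primary focus". The form of the time effect is left to be settled in modelling. Main effects of treatment and time are also to be estimated, without primary status.

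Under Effect Size and Sample Size, "The sample size estimate has been calculated to test for a linear group-by-time interaction" over six measurements. The target is a 2.5-drink decrease, with SD 5.2, within-person correlation .52, 1% type I error, 90% power and 10% attrition, giving 145 per group.

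Under Primary Outcome Measure, each report asks for "the highest number of alcoholic drinks consumed in a single occasion in the past week", and it is "collected in the 11 am (next-day) survey on Sunday mornings each week during the 6-week study period (total of 6 measurements"). The EMI and EMA arms complete "self-reported mobile phone–delivered surveys on Friday and Saturday nights for 6 weeks", and EMI messages answer those surveys. The first Sunday report therefore already follows two intervention nights.

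A telephone baseline questionnaire is described under Recruitment and Screening. The article neither counts it among the six measurements nor names it as a time point or covariate in the primary model.

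**The concern.** A group-by-time interaction asks whether the two arms' curves are parallel. If every point on those curves lies after the start of intervention, a difference that exists at the first point and stays the same leaves them parallel. All of it falls in the group term and none in the interaction.

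Such a pattern is plausible here. The Introduction says that what sets this kind of intervention apart is "the act of interrupting the drinking event in the moment it occurs", a mechanism that could work on the first weekend. A trial in which EMI participants drank 2.5 fewer drinks at their peak in every one of the six weeks could then fail its primary test. If the effect were largest at first and then waned, the interaction would point against EMI even though that arm drank less throughout.

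**Working it through.** **Inputs from the article:** difference 2.5 drinks, SD 5.2, r = .52, alpha 1%, power 90%, attrition 10%, six measurements, 145 per group.

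**Assumptions:** two-sided test, compound symmetry, equally spaced reports, attrition as complete loss (145 × 0.9 ≈ 130 evaluable per arm).

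**1. The plan's own figure.** For a slope test, n = 2(z₁ + z₂)² × SD² × (1 − r) / (Sxx × slope²), with z₁ = 2.576, z₂ = 1.282, and Sxx = 17.5 for six weekly points.
- Slope 2.5/6 per week: n = 128, or 143 after dividing by 0.9. This agrees closely with 145.
- Slope 2.5/5 per week (no difference at report 1, 2.5 at report 6): n = 89, or 99. This does not match.
- Plain comparison of two means: 2(z₁ + z₂)² × 5.2² / 2.5² gives 129, or 144. The exact t-test gives 131, or 146. Both agree closely.

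So 145 fits a slope that starts from zero one week before report 1, and fits a simple difference in level just as well.

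**2. Standard errors at 130 per arm.**
- Slope: per-person variance 5.2² × 0.48 / 17.5 = 0.742. SE of the difference = √(2 × 0.742 / 130) = 0.107.
- Six-report average: per-person variance 5.2² × (1 + 5 × 0.52) / 6 = 16.22. SE = √(2 × 16.22 / 130) = 0.500.
- Average adjusted for a baseline measure correlated .52 with each report: 16.22 − (0.52 × 5.2)² = 8.91. SE = 0.370.
- Joint 2-df test: under compound symmetry the two contrasts are uncorrelated, so the non-centrality is the sum of their squared standardised effects. The 1% critical value is 9.21.

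**3. Power by time course of the difference.**

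| Report 1 → report 6 | Slope per week | Average | Interaction | Average, unadjusted | Average, adjusted | Joint 2-df |
|---|---|---|---|---|---|---|
| 0.42 → 2.5 | 0.417 | 1.458 | 91% | 63% | 91% | 98% |
| 1.25 → 2.5 | 0.250 | 1.875 | 41% | 88% | 99% | 94% |
| 2.5 → 2.5 | 0 | 2.5 | 1% | 99% | >99% | 98% |
| 2.5 → 1.25 | 0.250, against EMI | 1.875 | 41%, wrong sign | 88% | 99% | 94% |

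Example for the joint test, row 1: (0.417/0.107)² + (1.458/0.500)² = 15.2 + 8.5 = 23.7, giving 98%. Row 3: 0 + 25.0, giving 98%.

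In the constant case, 10,000 simulated trials rejected 0.9% of the time for the interaction and 99.1% for the average.

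**4. Can the open choices rescue the test?**
- Time as a categorical factor over the six reports (5 df): still 1% for a constant effect.
- A larger sample: the article reports 601 recruited, about 200 per arm or 180 after 10% loss. The constant case stays at 1%; the half-present case rises from 41% to 57%.
- Baseline added as a seventh, equally spaced point (same item, SD and r assumed): for a constant effect the slope is 2.5 × 3 / 28 = 0.268 with SE 0.084, so linear power is 72%. It is 88% at 180 per arm. A categorical interaction (6 df) has 95% at 130 per arm.

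**The case against.** The best defence is that baseline may be intended as time zero. The article warns that moving from telephone to web may bias responses, which matters most if baseline and later values are compared. It also states its hypothesis as a decrease, and the slope that reproduces 145 starts from zero before report 1. A reader might therefore go too far in saying that baseline is definitely excluded: the article is silent, and the full protocol may settle it. What stands is that six Sunday measurements are specified, and that a linear interaction with baseline added still falls short of the planned 90% for a constant effect.

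Three other tempting readings go beyond the text.
- **That the outcome is defined as a six-week average.** It is worded as a change or reduction, which suits a slope as well as an average. Outcome, sizing and analysis can be read consistently.
- **That an immediate effect is the only natural expectation.** The description of the EMI arm also has next-morning messages that prompt reflection on future behaviour, which favours a gradual effect. Nothing in the article predicts fading; that row shows only how the test would behave.
- **That an early effect would go unreported.** The treatment main effect will be estimated. It lacks primary status, however, and promoting it after a null interaction would be a post hoc switch.

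The past-week recall could also let report 1 reflect a night before the first Friday. This could leave only a trace, since the intervention nights were chosen as the most popular drinking nights.

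**Conclusion.** The point holds for the declared primary test as written. That test detects a gradual build-up at the planned power (91%), loses more than half of it if half the effect is present at report 1 (41%), and has none beyond the error rate (1%) if the full effect is present at report 1 and sustained. The last result is exact and does not depend on sample size or on the form given to time over the six reports. The other figures rest on the plan's SD, correlation and alpha, and on the assumptions of a two-sided test, compound symmetry and 130 evaluable per arm.

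Blindness is complete only for a constant effect; partly early effects lose power by degrees. Because the article supports both mechanisms, a primary test that succeeds under only one of them is badly chosen.

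**What to change.** Before outcomes are examined by arm, make the primary EMI versus attention control test the joint 2-df test of group and group-by-time in the same mixed model, with the form of time (for example, linear in week) fixed in advance. Report the difference averaged over the six Sunday reports as the effect estimate. The cost is wording only. The drawback is that a 2-df test has no direction, so the averaged estimate must supply it.

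Alternatively, make the six-report average difference primary, adjusted for drinking collected at baseline, and keep the linear interaction as secondary. Secondary drinking measures are collected at baseline, but their correlation with weekly peak drinks is not given. Under slow build-up this contrast has 63% power unadjusted, against 91% for the slope; it reaches 91% only if the baseline measure correlates at about .52, which is an assumption.

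If baseline is meant to be time zero, say so, name the item, and use categorical time, since the linear interaction would have only about 72% power for a constant effect.
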